#### Randomization

For implementation of the RCT we will prepare the eligible list of participants after household screening, followed by individually randomizing the total participants into control and intervention groups [15]. Randomized participants in the treatment arm will get exposure to the GNG game as part of the encouragement design, while the participants randomly assigned to the control arm will not get any additional encouragement to download or play the game. (See Fig. 1) Researchers will not be blinded to the treatment condition assigned to individual participants [16].

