#### Encouragement design

Ten weeks of encouragement activity will be designed for participants to download and play the game with continuous nudges in the form of phone calls and WhatsApp messages (see Table 1), as well as follow-up scripted phone calls from the program facilitators.

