## Baseline and follow-up survey tools

### Quantitative survey

After completing the household listing exercise, the eligible participants will be identified and listed with the help of a screening tool. The final list of respondents will be prepared after de-identifying the individual participants into unique identification respondent IDs. For the main phase RCT study, we will recruit adolescent girls based on the previously mentioned inclusion criteria. The final list will be considered the sampling frame for the recruitment of baseline data collection. Once the sampling frame is developed, the eligible adolescent girls will be approached for data collection of in-person surveys.

The survey tool was prepared and tested in the pretesting of the method. There are eight sections in the baseline questionnaire and nine for the endline. (See Table 3).

**Table 3 Tab3:** Sections in the survey tool

Section	Theme	Description
I A	Household Characteristics	Details of household features, including understanding socio economic level of the household related to household goods/financial condition
I B	Individual Characteristics	Background information on age, siblings, parents, education, livelihood, friends, and career aspirations
II	Media and Technology	Phone and media consumption patterns
III	Health Services Utilization	Availability, accessibility, and preferences for healthcare services
IV	Menstrual Health and Fertility Awareness	SRH information/services received, perception, and attitude towards MHM
V	Empowerment and Aspirations	Understanding of personal aspirations, knowledge/attitudes about career aspirations, preparation for job/career, and financial independence
VI	Negotiation and Consent	Knowledge of attitudes and perceptions towards personal agency, consent in relationships, the legal age of marriage, and consent for sex
VII	Male and Female Relationships	Age-appropriate questions on types of relationships (platonic/physical), attitudes towards dating, perception of acceptable activities in a relationship
VIII	Contraception	Knowledge of methods of contraception, accessibility, and utilization
IX Only for endline survey	Knowledge, Attitude, and Practices: Go Nisha Go	Knowledge of GNG game, levels played, links accessed, product and brand recall, gameplay, and intention for behaviour change and measurement of confidence for negotiation with partner/parents

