#### Ethical consideration and consent/assent process

Prior to administering the survey, respondents will be asked for their consent, using standard format forms. Surveys will be administered in a private room/safe space in the participant’s residence/community and will last approximately 45–60 mins (based on our pre-testing experience). To protect participant privacy and ensure confidentiality, all Personally Identifiable Data (PID) will be appropriately stored and secured in accordance with the data security measures. All survey forms will only contain a unique ID code generated for the study.

Due to the sensitive nature of questions being asked, participants may feel personal discomfort, fatigue, or embarrassment during survey administration. Participants will be reminded that their participation is completely voluntary. They do not have to answer any question that they do not feel comfortable answering, and they can decide to end their participation in the study at any time. We do not anticipate respondents to be subjected to more than a minimal risk of discomfort from participating in this study. Additionally, our secure storage, encryption, and coding of all data, particularly PID, serves to minimize any risk of breaching confidentiality and compliance with local data privacy law.

Study participants will be able to access the game for free directly from their own Google Play Store account. Once downloaded the GNG game has clear terms of service that need to be accepted by the player, including preconditions for downloading the game if the person is under the age of 15. Participants who do not own their phones or share their phones with family members, may run the risk of backlash from male members/parents who may have reservations about access to SRH information among adolescent girls. In this regard, we will recruit credible community members and peers who are tasked to brief parents about the goal and objectives of the game, and the content will be aligned with the curriculum outlined in the government program for adolescents.

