#### Data security

To effectively monitor participants over the study period, identifiable data on participants’ demographic backgrounds, and personal contact information (household addresses, phone numbers, and e-mails) will be collected as part of the in-person survey. The data collected from in-person surveys will be administered in an electronic Computer Assisted in-Person Interview (CAPI) format, using the CSPro survey management system utilized by the U.S. Census Bureau [17]. Electronic survey data will be collected by interviewers on Android-based tablets, and data will be securely transferred from the Android tablets onto an Amazon Web Services (AWS) supported, secure, cloud server at the end of each working day. All Android tablets will be used for data collection only, and tablets’ settings will be adjusted so that field staff is blocked from accessing applications that are not applicable for data collection (e.g., internet browsing, social media, email). The AWS cloud server will be HIPAA-compliant and will meet all the necessary security requirements for storing Level 4 identifiable data. Once the data has been securely transferred to the cloud server, the survey record on the Android tablet will be immediately erased.

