### Follow-up survey

Following the ten-week intervention period/encouragement, participants will be assessed through the administration of the follow-up survey. All procedures related to informed consent, confidentially, data privacy, and risk mitigation will be followed, as will been done in the baseline. Resurveying participants in this manner will enable us to create a panel of individual girls, in which each girl is observed over two time points. In the endline survey, we will collect data using the same survey tool, with an additional section on gameplay and game-related elements, including brand recall of in-game links to products and services.

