Agency (decision making, negotiation, and consent)	Percentage of girls who/ have: - Gone to college on their own/alone, - Believe that “girls should make decisions for themselves”, - Believe that “girls can wear what they want”, - Believe that “girls should manage their own money”, - Believe that “girls should be financially independent”, - Believe that girls can talk to their parents when they were asked to marry a person whom they do not want to marry, - Feel confident to say no to a sexual act, - Feel confident to use condoms when her boyfriend is not willing to, - Think their boyfriend should always take consent for sex and refuse sex due to non-availability of contraception

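### Researchers are declared unblinded and no masking is described for the interviewers who collect the self-reported endline outcomes in person

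*Protocol article*

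**What the plan says.** The Randomization section states: "Researchers will not be blinded to the treatment condition assigned to individual participants". It makes no exception for the people who collect outcomes.

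Outcome data come from interviews. Under Data security: "Electronic survey data will be collected by interviewers on Android-based tablets". Under Follow-up survey: "In the endline survey, we will collect data using the same survey tool, with an additional section on gameplay and game-related elements". Table 3 lists that added section last, as Section IX, endline only, covering "Knowledge of GNG game, levels played, links accessed, product and brand recall, gameplay".

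Table 4 (Outcomes measures) defines the indicators as percentages of girls giving particular answers. They mix awareness and knowledge, reported practices, beliefs, and confidence, for example "Feel confident to say no to a sexual act".

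Three other statements bear on whether masking is feasible:
- The ethics section says "All survey forms will only contain a unique ID code generated for the study".
- The Encouragement design section assigns "follow-up scripted phone calls from the program facilitators". It does not say whether these people also conduct surveys.
- The Discussion accepts that self-report is best backed by observed measures.

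**The concern.** An interviewer who knows that a girl was encouraged can probe more, prompt, or code a borderline answer favourably. The Discussion says the study is expected to show gains, and that is the kind of expectation masking guards against. The interviewer need not intend any of this.

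Randomisation makes the girls in the two arms comparable, but it does not make the measurement comparable. Difference-in-differences cancels a bias that is the same at baseline and follow-up. It does not cancel one that appears in one arm after allocation. The Data analysis plan presents the unadjusted comparison as causal because assignment is random, and that also requires outcome measurement not to depend on arm.

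The one objective source, in-game data matched by profile code, exists only for girls who play. It cannot check answers from controls who do not.

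**Working it through.** **Inputs from the article.** 650 girls at each of 3 sites gives 1,950, and half gives 975 per arm (Sample size). The significance level is 0.05 (Data analysis plan), taken here as two-sided. The primary test is the time-by-arm interaction in a mixed logistic model.

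**Inputs not in the article.** Target difference, control rate, power, dropout and size of interviewer bias are not given. The sample size of 1,950 therefore cannot be reproduced, and it does not identify the effect sought. Several assumed designs land near 975 per arm:
- 30% v 36% at 80% power: 963
- 30% v 37% at 90% power: 954
- 50% v 56.5% at 80% power with continuity correction: 955

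**Step 1: endline comparison, no true effect, reporting-only shift b.** With an assumed rate p = 0.50:

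SE = √(2 × 0.50 × 0.50 / 975) = 0.0226, or 2.26 points.

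False-positive rate = P(|Z + b/SE| > 1.96).

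| Assumed rate | b = 2 points | b = 3 points | b = 5 points |
|---|---|---|---|
| 50% | 14% | 26% | 60% |
| 30% | 16% | 30% | 66% |
| 20% | 19% | 36% | 75% |

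At the 50% rate, a 1-point shift gives about 7%.

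**Step 2: shift that by itself reaches nominal significance at endline.** 1.96 × SE is 2.7 points at a 10% rate, 3.6 at 20%, 4.1 at 30%, 4.4 at 50% and 4.1 at 70%.

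**Step 3: closer to the planned test.** This is a linear-probability approximation to difference-in-differences at a 50% rate, with assumed within-person correlation ρ:

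SE(DID) = 2.26 × √(2(1 − ρ)) points; false-positive rate ≈ Φ(b/SE − 1.96).

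| ρ | SE (points) | Shift reaching significance | b = 3 points | b = 5 points |
|---|---|---|---|---|
| 0.2 | 2.86 | 5.6 | 18% | 42% |
| 0.5 | 2.26 | 4.4 | 26% | 60% |
| 0.7 | 1.75 | 3.4 | 40% | 81% |

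The planned analysis therefore does not protect against a shift that arises after allocation. How far the error rate rises depends on ρ, which the article does not give.

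**The case against.** The strongest reply is that the sentence speaks of researchers, while the article elsewhere names surveyors, interviewers, facilitators and field investigators separately. Endline interviewers may in fact be masked, and a condensed article can leave rostering and tablet settings to a field manual. The first part stands: a reader might infer that the interviewers are declared unblinded, but the text does not say so. What remains is an explicit waiver with no exception for outcome assessors and no masking described anywhere. If interviewers are masked, the sentence misleads and still needs a supplement.

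Other stronger readings also fail:
- **A bias as large as the effect sought.** A reader might infer this from the detectable differences at this sample size. No effect sought is stated and nothing sizes interviewer bias, so the comparison has no basis in the documents.
- **All outcomes equally exposed.** Five of the eight contraception indicators are comprehensive-knowledge items. These can be scored right or wrong and leave less room for expectation.
- **Facilitators already separate from interviewers.** The article does not say this, so separation has to be requested and cannot be assumed.
- **A certain upward bias.** This is the plausible direction, but it is not demonstrated.

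It is also fair to say that part of the protection is already in place, since forms carry only an ID and the game section is listed last. Masking interviewers cannot stop a girl who had ten weeks of calls and messages from answering to please or mentioning them.

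**Conclusion.** The point holds as a gap in protection against measurement bias. Researchers are stated to be unblinded, endline outcomes are self-reported in person, and no masking of the interviewers is described. It matters most for beliefs, confidence and reported practices.

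The size is conditional. At 975 per arm, a reporting-only endline difference of roughly 3 to 4 points is enough for nominal significance over most of the rates examined. The false-positive figures are sensitivity values resting on assumed rates, shifts and within-person correlations. They do not predict what will happen in this trial. No sample-size figure changes. The change should be made, but the article does not show that the results will be biased.

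**What to change.** Keep the statement that investigators are unblinded, since it may well be true of them, and add after it:

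> *Endline interviewers will not be told allocation. Tablets will show the respondent ID without arm. Staff who make encouragement calls will not conduct endline interviews. Section IX will be opened only after Sections I–VIII are completed and locked. Interviewers will record their guess of the arm before opening Section IX.*

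The recorded guess lets the trial report how well masking held and helps in judging the bias that remains. The cost is a change to tablet settings and less flexible rostering of existing staff. Sample size and survey content stay as they are, apart from the one added interviewer item.

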**Fig. 1 Fig1:**
[figure not shown]
Outcome Evaluation—Randomized Control Trial Study Design

#### Encouragement design

Ten weeks of encouragement activity will be designed for participants to download and play the game with continuous nudges in the form of phone calls and WhatsApp messages (see Table 1), as well as follow-up scripted phone calls from the program facilitators.

**Table 1 Tab1:**
[figure not shown]

[figure not shown]

[figure not shown]

[figure not shown]
Encouragement design for a ten-week intervention for GNG evaluation

#### Timepoint for tracking encouragements for participants

We will follow up with the participants by using a tracking sheet. Please see Table 2 for the schedule of enrollment,  implementation of encouragement, and assessments.

**Table 2 Tab2:** Schedule of enrolment, intervention, and assessment

Timepoint**	Study period*			
	Enrollment	Allocation	Post-allocation	
	−t_1_	0	t_1_	t_2_
Enrolment				
Eligibility screen	X			
Informed consent	X		X	X
Allocation		X		
Interventions: [Intervention: GNG game encouragement design]			↔	﻿↔
Control: No Encouragement				
Assessments: Baseline variables – indicators (see Table 3)			X	
Menstrual hygiene			X	X
Contraception			X	X
Agency (decision-making, negotiation, and consent)			X	X

*Recommended content can be displayed using various schematic formats. See SPIRIT 2013 Explanation and Elaboration for examples from protocols

**List specific timepoints in this row

## Baseline and follow-up survey tools

### Quantitative survey

After completing the household listing exercise, the eligible participants will be identified and listed with the help of a screening tool. The final list of respondents will be prepared after de-identifying the individual participants into unique identification respondent IDs. For the main phase RCT study, we will recruit adolescent girls based on the previously mentioned inclusion criteria. The final list will be considered the sampling frame for the recruitment of baseline data collection. Once the sampling frame is developed, the eligible adolescent girls will be approached for data collection of in-person surveys.

The survey tool was prepared and tested in the pretesting of the method. There are eight sections in the baseline questionnaire and nine for the endline. (See Table 3).

**Table 3 Tab3:** Sections in the survey tool

Section	Theme	Description
I A	Household Characteristics	Details of household features, including understanding socio economic level of the household related to household goods/financial condition
I B	Individual Characteristics	Background information on age, siblings, parents, education, livelihood, friends, and career aspirations
II	Media and Technology	Phone and media consumption patterns
III	Health Services Utilization	Availability, accessibility, and preferences for healthcare services
IV	Menstrual Health and Fertility Awareness	SRH information/services received, perception, and attitude towards MHM
V	Empowerment and Aspirations	Understanding of personal aspirations, knowledge/attitudes about career aspirations, preparation for job/career, and financial independence
VI	Negotiation and Consent	Knowledge of attitudes and perceptions towards personal agency, consent in relationships, the legal age of marriage, and consent for sex
VII	Male and Female Relationships	Age-appropriate questions on types of relationships (platonic/physical), attitudes towards dating, perception of acceptable activities in a relationship
VIII	Contraception	Knowledge of methods of contraception, accessibility, and utilization
IX Only for endline survey	Knowledge, Attitude, and Practices: Go Nisha Go	Knowledge of GNG game, levels played, links accessed, product and brand recall, gameplay, and intention for behaviour change and measurement of confidence for negotiation with partner/parents

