#### Outcomes measures

The baseline and follow-up survey tools are created with the previously tested tools from standard studies such as the UDAYA study (Understanding the lives of adolescents and young adults) [3], National Family Health Survey (NFHS) [18], Comprehensive National Nutrition Survey (CNNS) [19], Living Standards Measurement Study [20], and other national surveys in India [21]. The primary outcome of the evaluation is to measure improvement in the existing knowledge of MHM, contraception, and increased in agency for adolescent girls making informed decisions and choices in their lives (See Table 4). Several other secondary outcomes measuring intended behaviour change and agency with respect to improvement in decision making, choice of career, negotiation in relationships, and assertion of self-identity will also be evaluated.

**Table 4 Tab4:** List of selected outcome indicators for the study

Outcome indicators	Contents of measurement
Menstrual health management	Percentage of girls who have: - Received any information about MHM - Awareness about sanitary napkins - Awareness about different menstrual hygiene products - Obtained menstrual products alone - Practiced tracking their menstruation with comprehensive understanding of fertility awareness - Experienced trouble in obtaining menstrual hygiene products - Bought menstrual hygiene products online
Contraception	Percentage of girls who have: - Awareness about modern contraceptive methods - Comprehensive knowledge about Oral contraception pills - Comprehensive knowledge about Emergency contraception pills - Comprehensive knowledge about condoms - Comprehensive knowledge about IUD - Comprehensive knowledge about injectables - Practiced refusing sex due to non-availability of contraception - Awareness about condom’s use for prevention of pregnancy and/or infections

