#### Data analysis plan

Analyses will test whether participants who played the game (treatment arm) relative to control participants who have not received any encouragement to play the game:Improved knowledge about SRH care, including menstruation, menstrual hygiene, fertility awareness, and SRH/menstrual management products.Improved attitudes, confidence, and decision support for managing her self-care, SRH, negotiating consent and contraceptive use, and accessing/using DTC information, products, and care.Improved assertion of self-identity through DTC linkages to career, safety, and personal well-being resources, and improved self-efficacy.

Analysis of the quantitative study data will be conducted using STATA and SPSS where appropriate. Descriptive analysis will be performed for all variables, and unadjusted comparisons between experimental and control arms will be conducted. Descriptive statistics will be performed, including frequencies, means, and standard deviations. In addition, chi-square tests and t-tests will be used to examine associations in the data. A probability value of less than 0.05 will be considered statistically significant for all statistical tests conducted. Continuous variables will be tested for normality, and non-normal values will be categorised or transformed appropriately.

The following two analyses will be done to satisfy the objective of the study:Univariate descriptive analysis such as frequency, percentages, the mean, and standard deviation will be computed for different background characteristics and knowledge, attitude, and practice (KAP) variables.KAP variables will be analyzed using Z-test/t-test for encouragement and control arms in two points from the same respondent.The net change in KAP and its significance will be calculated using difference-in-difference (DID) analysis. The DID analysis will be done using the following formula. (See Table 5)

**Table 5 Tab5:** Difference-in-difference analysis pathway in RCT

	Experimental arm (s = 2)	Control arm (s = 1)	Difference (s)
Baseline (t = 1)	Y_12_	Y_11_	Y_21_ –Y_11_
Follow-up (t = 2)	Y_22_	Y_21_	Y_22_ –Y_12_
Difference (t)	Y_22_ –Y_21_	Y_12_ –Y_11_	Net change (DID) = (Y_22_ – Y_21_) – Y_12_ – Y_11_

The level of significance of DID will be tested using the below equation through regression analysis.$${\text{Y }} = {\text{ a }} + {\text{ b}}_{{{\text{1s}}}} + {\text{ b}}_{{{\text{2t}}}} + {\text{ b}}_{{{\text{3s}}*}}$$

where.

Y = dependent/response variable.

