a = constant.

s and t are study arm and time, respectively.

b_1_ and b_2_ are slopes for the study arm and time, respectively.

b_3_ = treatment effect.

s*t is a dummy variable indicating treatment status.

The significance level of the test will be measured using a p-value < 0.05 (95% level of significance as per the sample size estimation).

The primary comparison of the binary outcomes between intervention groups at baseline and follow-up will use mixed-effects longitudinal logistic regression, with random effects for the individual over time. The baseline will be included as a time point only. A categorical time effect will be used (profile model). A “difference-in-differences” analysis will compare the treatment arms. Statistically, this amounts to testing for an interaction between time and treatment arm in the longitudinal model. Since the treatment assignment is at random, this “unadjusted” analysis will provide a causal effect of the intervention. However, we will also conduct secondary analyses, adjusting for potentially relevant covariates (e.g., age, education, etc.), in addition to time and treatment arm, using backward model selection at the α = 0.15 threshold level. These secondary analyses may improve the precision (power) of estimating the treatment effect and reduce any bias due to random imbalances between arms.

The primary analyses will use an intent-to-treat approach and analyze all subjects according to a randomized group. For subjects missing the follow-up survey, we will impute data from the lower (worse) half of the distribution by the arm (conservative approach). We will also conduct dose analyses, in which we include only those subjects who complete the full intervention. Analyses will use data only for outcomes; (a) increased comprehensive contraceptive knowledge, (b) MHM (c) negotiation and self-efficacy. We will conduct exploratory analyses using outcomes.

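### Behaviour-change intention is placed only in the endline-only game section, so the planned arm-by-time effect cannot be estimated for it; for negotiation confidence, Table 3 conflicts with Tables 2 and 4

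*Protocol article*

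**What the plan says.** In the protocol article, under Quantitative survey, the text states: "There are eight sections in the baseline questionnaire and nine for the endline". Table 3 shows which section is added. Its last row, labelled "IX Only for endline survey", covers knowledge of the game, levels played, links accessed and brand recall, and ends with "intention for behaviour change and measurement of confidence for negotiation with partner/parents". The Follow-up survey section describes the endline as the baseline tool "with an additional section on gameplay and game-related elements, including brand recall of in-game links to products and services" and mentions neither intention nor confidence.

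These two measures are treated elsewhere as outcomes:

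- The evaluation framework section gives intended behaviour change as its third measurement aim.
- Outcomes measures announces "Several other secondary outcomes measuring intended behaviour change and agency with respect to improvement in decision making, choice of career, negotiation in relationships".
- The Data analysis plan says: "Analyses will use data only for outcomes; (a) increased comprehensive contraceptive knowledge, (b) MHM (c) negotiation and self-efficacy".
- The Discussion expects to show change in intended behaviours and in negotiation with a parent or partner.

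On method, the Data analysis plan says: "The net change in KAP and its significance will be calculated using difference-in-difference (DID) analysis". It then specifies a mixed-effects logistic model in which the treatment effect is the interaction of time and arm.

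**The concern.** A difference-in-differences compares change from baseline between arms, so the same item has to be asked at both waves. An item that appears only in Section IX has no baseline value, and the stated analysis cannot be run on it. A baseline not collected before the ten weeks of encouragement cannot be recovered later, and no analysis plan written afterwards can repair it.

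The placement raises a second question. Section IX is about the game. If its intention and confidence items were worded around the game, many control girls could not answer them in a comparable way, and even the endline comparison would lose its basis in randomisation.

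**Working it through.** **Step 1: when is each measure taken?**

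| Source | Behaviour-change intention | Negotiation confidence |
|---|---|---|
| Table 3, Sections I to VIII (both waves) | Not named | Not named; Section VI, on negotiation and consent, covers "Knowledge of attitudes and perceptions towards personal agency, consent in relationships, the legal age of marriage, and consent for sex" |
| Table 3, Section IX (endline only) | Named | Named |
| Table 2 (schedule) | No row | Agency row, which includes negotiation, marked at t1 and t2 |
| Table 4 (indicators) | No indicator | Two indicators under Agency: confidence to refuse a sexual act, and confidence to use condoms with an unwilling boyfriend |
| Outcomes measures | Secondary outcome | Negotiation named among the secondary outcomes; agency also part of the primary outcome |

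For intention, every source that mentions timing points to endline only. For confidence, Table 3 points one way and Tables 2 and 4 the other.

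**Step 2: is the arm-by-time effect identified?** Write the article's regression as Y = a + b1·s + b2·t + b3·s·t, with s and t recoded to 0/1 (this does not change the rank).

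- Both waves: the rows (1, s, t, s·t) are (1,0,0,0), (1,0,1,0), (1,1,0,0) and (1,1,1,1). The rank is 4 of 4, so b3 is identified.
- Endline only, t = 1 throughout: the rows are (1,0,1,0) and (1,1,1,1). The rank is 2 of 4. The model reduces to Y = (a + b2) + (b1 + b3)·s, so only the sum b1 + b3 can be estimated.

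The same holds for the linear predictor of the planned logistic model.

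**Step 3: what remains at endline?** Under random assignment b1 is zero in expectation, so b1 + b3 is a valid estimate of the effect, provided that all randomised girls are asked the same question. The article states no power or expected rates, so the following is an illustration. Assume two-sided 0.05, 975 per arm (2 × 975 = 1,950), no loss, and power = Φ(d/SE − 1.96), where SE = √[(p(1−p) + (p+d)(1−p−d))/975].

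- Control rate 20%, d = 0.0535: SE = √[(0.1600 + 0.1892)/975] = 0.0189; d/SE = 2.83; power is about 0.81. In steps of 0.05 points, this is the smallest difference that reaches 80%. For 90% it is 6.2 points.
- Control rate 50%: 6.35 points for 80% and 7.35 points for 90%.

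**Step 4: what would a baseline add?** For a linear analysis with equal variances and correlation ρ between waves (an assumption), the variance of the difference-in-differences relative to the endline comparison is 2(1 − ρ): 1.4 at ρ = 0.3, 1.0 at 0.5 and 0.6 at 0.7. With the baseline as a covariate the ratio is 1 − ρ²: 0.91, 0.75 and 0.51. So an endline-only item is not useless, but a baseline allows the stated analysis and can improve precision.

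**The case against.** The strongest reply is that Table 3 gives one-line section summaries, not an item list, and that the questionnaire is not shown. Some Table 4 indicators, such as tracking menstruation or buying products online, are also absent from the Table 3 wording, so silence about confidence in Section VI does not prove that no baseline item exists. Table 2 expressly schedules agency, including negotiation, at both waves, and Table 4 places confidence indicators in that domain. This stands. A reader might infer that negotiation confidence has no baseline at all; the documents do not support that, only that their tables disagree.

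The reply is weaker for intention. Sections I B and V cover aspirations and could hold related items, but no baseline section, Table 2 row or Table 4 indicator names intention, while Table 3 positively assigns it to the endline-only section.

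A reader might also infer that control girls will skip Section IX, leaving a comparison of self-selected players. No skip rule is stated, and nothing says that these items refer to the game. This is a risk raised by the section's theme, not an established defect.

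Finally, a reader might conclude that the trial can say nothing about intention. That goes too far. The Data analysis plan also foresees unadjusted comparisons between arms, and an endline comparison is protected by randomisation. The article does not, however, assign that comparison to these outcomes in place of the difference-in-differences.

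**Conclusion.** The point holds in two parts. For behaviour-change intention, a named objective and secondary outcome, the planned arm-by-time effect cannot be estimated as the article is written: 2 of the 4 model parameters are estimable, and the interaction is not among them. An endline comparison between arms is the only option left, and only if every girl in both arms is asked in wording that does not presuppose playing. For negotiation confidence, Table 3 contradicts Tables 2 and 4 on when it is measured, and the tables must be reconciled.

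This rests on reading the Section IX row as a true statement of where the intention items sit. If the full questionnaire also asks them at baseline, Table 3 needs correcting and the analysis stands. Because the gap affects a secondary outcome and one conflict between tables, the point is worth acting on but is less than a must-fix.

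**What to change.** 1. Put the intention and negotiation-confidence items in a section asked of every girl in both arms at baseline and endline, for example Section VI, worded without reference to the game.
2. Keep in Section IX only game-specific process items, such as levels played, links accessed and brand recall.
3. Correct Tables 2, 3 and 4 so that they agree on the timing of negotiation confidence, and give intention a row in Table 2.
4. For any item left at endline only, state a comparison of all randomised girls between arms at endline in place of the difference-in-differences.

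The cost is some reordering of the questionnaire and a few extra minutes in a baseline interview that already runs 45 to 60 minutes. No extra participants are needed. If baseline interviews are already complete, only items 3 and 4 remain open, together with neutral wording at endline.
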